## Abstract

**Introduction:**

Otitis media with effusion (OME) affects hearing, speech development, and quality of life (QoL) in children. The ‘Blow, Breathe, Cough’ (BBC) intervention promotes nasal, respiratory, and middle ear clearance through nose blowing, deep breathing, coughing, and hand hygiene. It shows promise in resolving OME but lacks randomized-controlled trial (RCT) evaluation. This paper presents a RCT protocol evaluating BBC's effect on OME resolution, hearing, speech, and QoL in children aged two to seven years.

**Methods:**

This parallel-group, 1:1, outcome assessor-blinded, individual adaptive RCT investigates whether completing the BBC intervention plus hand hygiene twice-daily at home increases OME resolution after 4-to-6 weeks in children with OME, compared to hand hygiene alone. Families (n = 250) perform their individually randomized program (BBC plus hand hygiene, or hand hygiene only) at home. The primary outcome is the difference in OME resolution rates between trial arms, assessed using tympanometry (type B to A or C_1_ transition) and otoscopy. Secondary outcomes include natural OME resolution, discharges from tertiary care, family satisfaction, hearing thresholds, QoL, bacterial load in the nasopharynx and on hands, cost comparison within the RCT versus standard care, and adverse events. All outcomes are measured by blinded researchers. An intention-to-treat analysis will be performed on all randomized participants. Guided by an Aboriginal Community Advisory Group, the RCT ensures culturally appropriate research whilst addressing community priorities in managing childhood ear disease.

**Discussion:**

If efficacious, BBC could reform OME treatment, reduce costs, and improve long-term hearing, speech, and QoL outcomes in some children. Its accessibility offers a globally scalable solution.

## What is known about this topic?

1

•Otitis media with effusion (OME) affects children's hearing, speech, and quality of life whilst straining the finances and resources of healthcare systems globally. Cost-effective, non-invasive solutions should be considered to reduce OME prevalence and address delays in otolaryngology care provision for OME.•Whilst currently recommended for OME prevention in Australia, a study interviewing Australian educators and primary health workers suggested the ‘Blow, Breathe, Cough’ intervention may resolve (treat) OME, although its use in treatment remains unvalidated through clinical trials.

## What does this paper add?

2

•This paper details the protocol of an adaptive randomized-controlled trial assessing the efficacy of the BBC intervention plus hand hygiene in resolving OME, allowing real-time adjustments to optimize trial efficiency.•If effective, the BBC intervention plus hand hygiene could reduce the need for surgical intervention in some children and reduce healthcare costs associated with OME, offering a scalable, non-invasive solution accessible across diverse settings globally.

## Introduction

3

### Background and rationale

3.1

The human ear, essential for hearing and balance, consists of the outer, middle, and inner ear [1]. The middle ear, including the tympanic membrane, ossicles, and Eustachian tube, facilitates sound transmission to the brain as electrical signals by matching impedance between the air-filled outer ear and fluid-filled inner ear [2]. Otitis media (OM) refers to an array of inflammatory middle ear conditions including otitis media with effusion (OME), where middle ear fluid builds up without acute infective symptoms, disrupting sound conduction and subsequently impairing hearing [3]. In metropolitan Western Australia, OM affects Australian Aboriginal (hereafter respectfully referred to as ‘Aboriginal’) children at a disproportionately higher rate [4]. Whilst 26.8 % of metropolitan Western Australian children are diagnosed with OM by age three years, around 50 % of Aboriginal children experience OM by just six months of age [5,6]. Hearing loss caused by OM can have severe long-term impacts on a child's speech, language, literacy development and behaviour, potentially affecting school readiness [[7], [8], [9]]. It is also associated with reduced school attendance rates for Aboriginal children [10], and is known to negatively influence the educational experience and academic performance of children, which may impact later educational or employment prospects [11]. OM places additional responsibilities, disruptions, and stress on families, with parents voicing particular concerns around its impact on their child's development [12]. As such, OM is a significant risk factor for compromised healthy childhood development, particularly among Aboriginal children [5,6,[13], [14], [15]].

A common treatment option for OME is the prescription of oral antibiotics, particularly for Aboriginal children in remote areas; however, their efficacy may be outweighed by side effects such as diarrhoea, vomiting, and skin rashes, as well as growing concerns around antibiotic resistance [16,17]. The surgical insertion of tympanostomy tubes to aerate the middle ear can improve short-term hearing and reduce OME-related complications; however, they carry risks such as anaesthetic-related issues and tympanic membrane damage, and their long-term benefits remain unclear [14,18,19]. Hearing aids for OME-related hearing loss can also be offered in circumstances where surgical options (such as tympanostomy tubes) are not suitable, are declined, or are ineffective [20]. However, their use remains low amongst Aboriginal children, largely due to the peer-related stigma and negative perceptions associated with hearing aid use [21]. Whilst cost is not always the primary barrier to accessing treatment for OME in Australia, socioeconomic disadvantage experienced by families can significantly impede timely and equitable access to quality otolaryngology care [22]. Contributing factors include challenges navigating the healthcare system, lack of primary care continuity, limited health literacy, and lower uptake of preventative ear health services.

Children requiring tertiary otolaryngology care in Australia endure wait times often exceeding twelve months, with an additional wait of between six and twelve months for surgical treatments such as tympanostomy tube insertion [23]. Annually, treatment costs for all forms of OM are estimated between $100–400 million Australian dollars (AUD) in Australia (approximately $62.8 - $251.3 million United States dollars [USD]), and $5 billion USD in the United States [24,25]. Given OM's substantial impact on childhood development and the strain it imposes on global healthcare systems that precipitates treatment delays, interest is growing in exploring cost-effective, non-invasive solutions to reduce its prevalence and improve outcomes for children with OME [[24], [25], [26], [27]].

The 'Blow, Breathe, Cough’ (BBC) intervention is a simple, freely available, school and family led health promotion intervention encouraging children to blow their nose, breathe deeply, cough, and practice good hand hygiene to assist nasal and respiratory secretion clearance, ultimately encouraging middle ear fluid drainage [28]. Although used anecdotally since the 1970s in Australian classrooms, primary care settings, and Aboriginal community health organizations to prevent ear disease, the BBC intervention plus hand hygiene lacks robust evidence on its efficacy [29]. Findings from interviews with Australian educators and primary healthcare workers suggest the BBC intervention plus hand hygiene may reduce OME and improve hearing in children, decrease the incidence of ear infections, and increase knowledge and awareness of positive hygiene practices [29,30]. Additionally, a non-randomized controlled trial conducted in a school setting demonstrated a statistically significant reduction in signs of upper and lower respiratory tract disease following a daily program of nose blowing, deep breathing, coughing, and exercise among Aboriginal children, although maintaining daily compliance was challenging due to inconsistent school attendance [31]. Considered together, these studies provide preliminary support for evaluating the treatment efficacy of the BBC plus hand hygiene intervention in resolving OME using a randomized-controlled trial (RCT) in a home-based setting. This paper details the protocol for a RCT that will examine the efficacy of the BBC intervention plus hand hygiene in resolving (treating) OME in children in a home-based setting and its impact on hearing, speech, and quality of life (QoL) outcomes.

## Methods

4

### Study design

4.1

This parallel group, 1:1, outcome assessor-blinded, individual adaptive RCT asks the following question: *‘Among children aged two to seven years with OME accessing pediatric otolaryngology services, does completing the BBC intervention plus hand hygiene at least twice daily, compared to hand hygiene alone, in a home-based setting increase the proportion of children experiencing OME resolution after four to six weeks?’* This interventional study is a parallel-group, adaptive RCT which employs a two-arm design (the BBC program plus hand hygiene as the intervention, and a hand hygiene only program as the control), featuring a randomization allocation of 1:1 and blinded outcome assessments. As an adaptive RCT, it allows for modifications to procedures based on interim analysis results [32]. The protocol for the RCT is structured in accordance with the Standard Protocol Items: Recommendations for Interventional Trials (SPIRIT) 2013 Statement and RCT results will be reported following the CONSORT 2010 statement for reporting parallel group RCT's [33,34]. This RCT has been registered with the Australian and New Zealand Clinical Trials Registry (ANZCTR) (No. ACTRN12622000546752).

### Study setting and sites

4.2

Participants are recruited through three pathways: i) children referred to otolaryngology and audiology departments of pediatric hospitals in Western Australia, ii) children referred for surgical intervention for OME (e.g. tympanostomy tube insertion) at pediatric hospitals in Western Australia, and iii) children referred to the Djaalinj Waakinj Centre for Ear and Hearing Health (hereafter referred to as ‘Djaalinj Waakinj’). Recruitment from Western Australian pediatric hospitals will occur primarily at Perth Children's Hospital (PCH) in Nedlands, Western Australia. Meaning ‘listening and talking’ in Aboriginal Noongar language, Djaalinj Waakinj is a service developed with the local Aboriginal community to provide timely diagnosis and intervention for Aboriginal children with ear and hearing issues in southern metropolitan Western Australia [35,36].

### Eligibility criteria

4.3

Children and their families need to meet all the following inclusion criteria to participate:1.Aged between two and seven years old.2.Clinical referral indicates hearing or ear related concerns.3.Able to attend all study visits regardless of residential location within Western Australia.4.Persistent OME, defined as two type B tympanometry results documented by a health professional at least three months apart within a 12-month period in the same ear (unilateral or bilateral), with or without hearing loss. These results can be sourced from the child's medical records or collected during screening visits for the RCT. Inclusion of children with persistent OME aligns with the 2020 Otitis Media Guidelines, which recommend intervention when OME persist for three months or longer [4]. To determine eligibility based on persistent OME, children and their families are offered up to three screening visits.

Children and their families are excluded if any of the following exclusion criteria are met:1.Scheduled to undergo surgical intervention for OME within the next four weeks.2.Current or previous diagnosis of cleft lip and/or palate, Down syndrome, major chromosomal anomalies, craniofacial anomalies, chronic suppurative otitis media, or congenital ear anomalies.3.Concurrent participation in another interventional ear study.4.Unable to engage with study procedures due to any physical, medical, developmental, behavioral or cognitive condition(s).5.Parent(s)/carer(s) decline to cease using non-study ear clearing interventions during the intervention or control period (any ear treatments that are not clinically prescribed).6.Clinical inclusion criteria for persistent OME are not met (inclusion criteria no. 4 above).7.Share a household with a current or previously participating child.

### Interventions and comparators

4.4

This study has two arms: the BBC program intervention plus hand hygiene, and a hand hygiene only program control. Families in the intervention arm receive the BBC intervention routine (Fig. 1) to perform at least twice daily for four-to-six weeks, which incorporates the hand hygiene program steps (Fig. 2) [28,37]. The control arm families receive a hand hygiene program in line with Centers for Disease Control and Prevention guidelines, for completion at least twice-daily for four-to-six weeks (Fig. 2) [37]. Trained research staff deliver both programs by conducting interactive demonstrations using step-by-step guides and checklists, and by providing educational materials containing visual prompts to guide program completion. Both arms receive watchful waiting, supportive care, and ear health education (Table 1) [17,38]. Use of ear-specific treatments (e.g. ear candles, EarPopper®, nasal sprays etc.) are prohibited during the four-to-six-week intervention/control period to avoid contamination of the assigned program, with any use of these monitored at each study visit by collecting updated medical histories (Table 2). Adherence is tracked through weekly text message surveys regarding program completion frequency (Table 2). Hand hygiene is recommended by the National Health and Medical Research Council (NHMRC) *Staying Healthy* guidelines to reduce the spread of communicable disease in children, and is embedded within the BBC intervention [39]. It was selected as the control to isolate the effects of blowing the nose, breathing, and coughing on the presence of middle ear fluid whilst engaging control group families in a beneficial, evidence-based hygiene practice [4,29].

**Fig. 1 fig1:**
[figure not shown]
Steps for the ‘Blow, Breathe, Cough’ intervention [28].

**Fig. 2 fig2:**
[figure not shown]
Steps for the hand hygiene program [37].

**Table 1 tbl1:** Explanation of additional care provisions within study arms.

**Watchful waiting**	Conducting ear and hearing health assessments at scheduled and as needed time points, with care escalated as clinically indicated.
**Supportive care**	Encouraging parent/carer(s) to raise any questions or concerns about their child's ear health with the research team during study appointments or via phone/text message and to arrange an unscheduled visit as needed or clinically appropriate.
**Generic ear health education resources**	Provision of an information sheet published by the Child and Adolescent Health Service about glue ear (OME).

**Table 2 tbl2:** Data collection timepoints.

Timepoints	Week 0	Weeks 4–6	Weeks 24–32	Any timepoint
	ScreeningEnrolment	Post-randomization	Final follow-up	Unscheduled visit
Informed consent	•			
Eligibility	•			
Randomization	•			
Medical history	•	•	•	•
Family history	•	**×**	**×**	**×**
Sociodemographic data	•	**×**	**×**	**×**
Otoscopy	•	•	•	•
Tympanometry	•	•	•	•
Audiometry	•	•	•	•
OAE	•	•	•	•
OM-6	•	•	•	•
PLUM	•	•	•	•
HATS	•	•	•	•
Adherence survey (via SMS)	Administered weekly between timepoints			
Intervention program performance checklist	•	•	**×**	**×**
Intervention program parent/carer understanding checklist	•	**×**	**×**	**×**
Motivational outcomes		•	•	**×**
Nasopharyngeal and palm specimen	•	•	**×**	**×**
Adverse event monitoring	Continuous			

• - mandatory; **× -** optional.

### Outcomes

4.5

The primary outcome measure is the proportion of children that experience OME resolution in the intervention arm compared to the control arm, assessed through tympanometry. Tympanometry is a diagnostic test of middle ear function using parameters such as peak pressure, compliance, and ear canal volume, which tracks the transition from type B result (indicative of OME) at enrolment (week 0) to a type A result (normal) or type C_1_ result (Eustachian tube dysfunction, suggesting resolving OME) at post-randomization (week 4-to-6) (Table 2) [30,40]. For this study, a type A tympanogram is defined as a peak pressure of > −100 daPa, a type B tympanogram has an indeterminable peak pressure, a type C_1_ tympanogram as a peak pressure of between −100 and −199 daPa, and a type C_2_ tympanogram as a peak pressure of −200 to −400 daPa [41]. Type C_1_ tympanograms will be considered indicative of resolved OME in addition to type A tympanograms, as the literature suggests type C_1_ may reflect a transient or resolving stage of middle ear effusion, rather than a persistent form of OME requiring intervention [16,41]. Resolution can be unilateral or bilateral, however the primary outcome will only be considered in any ears that produced type B tympanograms at enrolment. Type C_2_ tympanogram findings will be considered indicative of ongoing middle ear dysfunction. The efficacy of the BBC intervention will be considered clinically meaningful if it results in a number needed to treat to benefit (NNTB) of 10 or less for the resolution of OME.

Secondary outcome measures include: (1) rate of natural OME resolution, evidenced by a transition of type B tympanograms to type A or C tympanograms; (2) proportion of otolaryngology/audiology care discharges, evaluated using multidisciplinary team (MDT) and clinician review outcomes from enrolment to final follow-up (weeks 24-to-32); (3) family satisfaction with care provision through the RCT, assessed using a survey at final follow-up, (4) four-frequency hearing thresholds measured by audiometry at enrolment, post-randomization, and final follow-up; (5) QoL, assessed through the Otitis Media-6 (OM-6), Parent-evaluated Listening and Understanding Measure (PLUM), and Hearing and Talking Scale (HATS) questionnaires at enrolment, post-randomization, and final follow-up; (6) bacterial loads, quantified as the densities of all bacteria species of interest at enrolment and post-randomization, analyzed using high-throughput qPCR on samples collected from the nasopharynx and palms of hands; (7) cost-of-service comparison for OME diagnosis and management through the study compared to standard care via economic analysis; and (8) the proportion of adverse events, monitored through safety data collection from enrolment to final follow-up. Refer to Table 2 for a comprehensive schedule of data collection methods and collection timepoints for participants in both trial arms.

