### Sample size

4.6

Power analysis was used to understand the trial operating characteristics, assuming a range for the proportion of OME resolution in the control arm to be between 14 % and 20 % [16]. Assuming a moderate 13 % absolute increase in OME resolution at post-randomization in the intervention arm compared to the control arm and type one error controlled at 5 %, the power is estimated to be approximately 80 % for a maximum sample size of 250 participants. Accounting for 10 % loss-to-follow-up, the RCT intends to recruit up to 275 participants to achieve sufficient power to declare superiority of the BBC intervention plus hand hygiene.

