### Allocation-sequence generation, concealment, randomization, and blinding

4.8

Participants are randomly assigned to the intervention or control arm using a computer-generated list (R v4.1, block sizes 2, 4, 6, 8) [45], stratified by site (PCH, Djaalinj Waakinj, or other Western Australian hospital sites), OME class (unilateral or bilateral), and prior tympanostomy tube insertion (yes or no) (Fig. 3).

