### Primary and secondary statistical methods

4.10

A Bayesian logistic regression model will be used for the primary analysis on the binary endpoint $Y_{i}\in \left\{0,1\right\}$ for participant i=1,2,…,N. Currently, there are two arms and three recruitment pathways, however the model is designed to allow additional arms or recruitment pathways to be introduced in the future. A participant may be randomized to arm j=0,1,…,J (where j=0 is the control arm and j=1 is the intervention arm) and be recruited via pathway r=0,1,…,R (where r=0 is the PCH otolaryngology/audiology outpatient departments, r=1 is the PCH otolaryngology surgical pathway, r=2 is Djaalinj Waakinj and r≥3 for other approved sites). Let $x_{i}$ and $\omega_{i}$ be vectors of length J and R and contain the arm allocation and recruitment pathway, respectively, for participant i. Here, $x_{ij}=1$ if participant i is allocated to arm j and $x_{ij}=0$ otherwise. Similarly, $\omega_{ir}=1$ if participant i is recruited via recruitment pathway r and $\omega_{ir}=0$ otherwise. We use a Bernoulli model with a logistic link function below:$$Y_{i}∼\text{Bernoulli}\left(\text{logi}t^{-1}\left(\pi_{i}\right)\right)$$$$\pi_{i}=\alpha +\sum_{j=1}^{J}x_{ij}\beta_{j}+\sum_{r=1}^{R}\omega_{ir}\gamma_{r}$$

Here, $\pi_{i}$ is the log odds of OME resolution between 4 and 6 weeks post-randomization for participant i. The log odds for a participant allocated to the control arm and recruited via the PCH otolaryngology/audiology outpatient pathway is α, and $\beta_{j}$ and $\gamma_{r}$ are the adjusted log odds ratios of arm j compared to the control arm and recruitment pathway r compared to the PCH otolaryngology/audiology outpatient pathway, respectively. We assign the following weakly informative prior probability distributions to the model parameters:$$\alpha ∼N\left(\text{logit}\left(0.17\right),0.3^{2}\right)$$$$\beta_{j},\gamma_{r}∼N\left(0,1\right)\;\forall j=1,\ldots ,J,r=1,\ldots ,R$$

The posterior distribution of the quantity of interest ($\beta_{1}$) will be estimated from the primary analysis and will be used to inform trial adaptation decisions.

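### Section 4.5 does not fix how a child with two type B ears is scored, and the control rate, effect and intercept prior are not tied to either scoring rule

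*Protocol article*

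**What the plan says.** Section 4.5 (Outcomes) makes the child the unit: "The primary outcome measure is the proportion of children that experience OME resolution in the intervention arm compared to the control arm, assessed through tympanometry". It then turns to ears: "Resolution can be unilateral or bilateral, however the primary outcome will only be considered in any ears that produced type B tympanograms at enrolment".

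Bilateral children are expected. Section 4.3 (Eligibility criteria) accepts persistent OME "in the same ear (unilateral or bilateral), with or without hearing loss", and section 4.8 stratifies randomisation by unilateral or bilateral OME. The share of bilateral children is not given.

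Section 4.10 says of the model: "A Bayesian logistic regression model will be used for the primary analysis on the binary endpoint", with a single outcome per participant. The linear predictor contains arm and recruitment pathway, but not OME class. The intercept prior is normal, centred on logit(0.17) with SD 0.3.

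Section 4.6 assumes a 14-20% control rate and a 13-point increase. It reports type I error controlled at 5% and about 80% power "for a maximum sample size of 250 participants". It does not say whether these rates are per ear, any-ear or all-ears.

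**The concern.** The laterality sentence says which ears are examined and that one or both may resolve. It does not say how two ears become one outcome. For a unilateral child the question does not arise. For a bilateral child with one cleared ear, the outcome is 1 under any-ear and 0 under all-ears.

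The stopping rules in section 4.11 act on the treatment coefficient for this outcome. The coefficient has a definite meaning only once the outcome is defined. The two rules also give different child-level control rates, and the intercept prior pulls the control rate towards 17% whichever rule is used. The operating characteristics can therefore move with the scoring rule, and so can the comparison with the section 4.5 threshold of a number needed to treat of 10 or less.

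**Working it through.** **The plan's own figure.** Take 125 children per arm and 17% v 30%. The pooled SE is √(2 × 0.235 × 0.765 / 125) = 0.0536 and the unpooled SE is √((0.17 × 0.83 + 0.30 × 0.70) / 125) = 0.0530.

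- Two-sided 5%: (0.13 − 1.96 × 0.0536) / 0.0530 ≈ 0.47, power 68.1%.
- One-sided 5%: (0.13 − 1.645 × 0.0536) / 0.0530 ≈ 0.79, power 78.5%.
- Documented Bayesian rule (looks at 100, 150, 200 and 250; superiority above 0.975, futility below 0.05): simulated power 66-69% at 17%, and 62-75% over control rates of 14-20%. Type I error is 0.3-2.4% over that range.

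The 5% ceiling therefore holds at 14-20%. The 80% is matched only by a fixed one-sided test at the lower control rates, which is a separate matter. The baseline for what follows is about 68%, not 80%.

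**From ears to children.** With per-ear rate p and within-child correlation ρ:

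- both ears clear: p₁₁ = p² + ρp(1 − p)
- at least one clears: 2p − p₁₁
- trial rate with bilateral share s: (1 − s)p + s × (bilateral rate)

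Assumptions that the article does not give: 17% and 30% are per-ear rates; s = 50-75%; ρ = 0.2-0.5.

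Bilateral controls at ρ = 0.2: p₁₁ = 0.0289 + 0.2 × 0.1411 = 0.057, any-ear 0.283. At ρ = 0.5: p₁₁ = 0.099, any-ear 0.241. So 24-28% resolve under any-ear and 6-10% under all-ears.

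Bilateral intervention children at ρ = 0.2: p₁₁ = 0.09 + 0.2 × 0.21 = 0.132, any-ear 0.468. At ρ = 0.5: p₁₁ = 0.195, any-ear 0.405.

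| | Any-ear | All-ears |
|---|---|---|
| Control, s = 0.5, ρ = 0.5 | 20.5% | 13.5% |
| Intervention, same | 35.3% | 24.8% |
| Control, s = 0.75, ρ = 0.2 | 25.5% | 8.5% |
| Intervention, same | 42.6% | 17.4% |
| Difference, points | 14.7 to 17.1 | 11.3 to 8.9 |
| Number needed to treat | 6.8 to 5.8 | 8.9 to 11.3 |
| Power, documented rule | about 80-94% | about 18-49% |
| Type I error, documented rule | about 2.5-6.5% | below 1% |

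The last two rows are simulated with the article's priors and rules. A separate simulation with s = 40-80% and ρ = 0.3-0.7 gave power of 74-95% v 17-59% and type I error of 1.8-6.7% v 0-0.9%.

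**Why type I error moves.** The prior's 95% range for the control rate is logit(0.17) ± 1.96 × 0.3 = −1.586 ± 0.588, or about 10% to 27%. Its precision is 1/0.3² = 11.1. One control child at 17% contributes 0.17 × 0.83 = 0.141, so the prior weighs about as much as 11.1/0.141 ≈ 79 control children (ignoring pathway terms). When the true control rate is above 17%, part of the excess in the intervention arm is credited to treatment. Simulated type I error is about 0% at a 10% control rate, 1.0-1.3% at 17%, 5.2-6.8% at 25% and 9-13% at 30%. It passes 5% at about 23-25%.

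**If the rates belong to the other scoring rule** (s = 60%, ρ = 0.5):

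- 17% v 30% set as all-ears, any-ear scored: control rate 27.4%, type I error 7-9%.
- 17% v 30% set as any-ear, all-ears scored: 10.0% v 18.9%, power 17-24%, type I error below 0.1%.

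**If 17% v 30% are child-level rates under the rule actually used:** nothing shifts, and power stays at about 68%.

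**Adding OME class.** In simulations on the per-ear assumption, adding the class term brought type I error back to about 2% under any-ear and recovered much of the lost power under all-ears.

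**The case against.** The wording favours any-ear, and nothing in the article positively supports all-ears, to which the low power belongs. Under any-ear on the per-ear assumption, power is at or above the stated figure, and type I error passes 5% only where the bilateral share is high and the ear correlation low. This stands. It limits the harm under the likelier reading, but it does not settle the rule.

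The per-ear reading of 17% v 30% is an assumption. The outcome is a proportion of children, so the rates may already be child-level. The per-ear conversion also changes the 13-point difference, to 15-17 points or 9-11 points, so part of the power gap is a changed effect size. This stands too, and it makes the size conditional.

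A reader might go further in four ways that the documents do not support:

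- **That the stated 80% and 5% must change with the scoring rule.** They need not, if they were set for the intended rule.
- **That the same data would give opposite superiority decisions.** Only power under each rule was computed, not disagreement within a trial.
- **That inclusion criterion 4 makes all-ears the correct rule.** It defines persistent OME for entry, by two type B results in one ear at least three months apart. It does not define resolution.
- **That the rule will be chosen after interim results are seen.** The full protocol and analysis plan are not shown and may already fix it.

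**Conclusion.** The point holds as a gap in the definition of the primary endpoint. The article addresses laterality but does not fix the score of a bilateral child, and it ties neither the design rates nor the prior to a scoring rule.

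The size depends on what 17% v 30% means. As per-ear rates, with the assumed bilateral share and correlation, the choice separates power of about 80-94% from about 18-49%, and type I error of about 2.5-6.5% from below 1%. As child-level rates under the intended rule, there is no shift from about 68% power. The type I effect comes from the tight intercept prior meeting a different control rate; a conventional fixed test would keep its level under either rule. The finding is worth acting on because this endpoint drives adaptive stopping and the remedy is cheap.

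**What to change.** Before the first interim analysis:

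1. State in 4.5 whether a child with two type B ears at enrolment counts as resolved when either ear clears or only when both do. The choice is the sponsor's.
2. State in 4.6 and 4.10 that the control rate, the 13-point increase and the prior centre refer to that rule. Re-centre the prior if they do not.
3. Add OME class to the primary model. It is already a randomisation stratum, and the child-level rate differs by class under either rule; without the term, the tight intercept prior carries that difference into the treatment coefficient. The prior centre must describe the reference class: unilateral, if 17% is a per-ear rate. With the other class as reference, the mismatch remains.
4. Re-run the simulation with that rule and model, and restate power and type I error in 4.6.
5. Report the other scoring rule, or an ear-level model with a child random effect, as a supporting analysis.

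Cost: a few sentences, one model term and one simulation run. No new data are needed. The covariate costs some nominal power under any-ear. If all-ears is chosen and the design rates prove to be per-ear, the restated power may be low enough to reopen the sample size.
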